### Patient recruitment

Potential patients will be identified via a variety of mechanisms, including sourcing a daily list of INR results from the hospitals' pathology services; written or verbal communication of the details of patients on warfarin from pharmacy staff to project officers; and liaison with nursing staff on key wards (e.g. coronary care units, cardiothoracic surgery units) from where the majority of patients are expected to be recruited.

### Control patients

Potential control patients will be approached prior to discharge and informed consent obtained for involvement in the study using standard Information Statements and Consent Forms. Informed consent will also be obtained from patients' GPs. Baseline data will then be collected during the patients' admissions and immediately after discharge.

After discharge from hospital, control patients will receive 'usual care' according to their community healthcare provider's usual practice. No restrictions will be based on usual care, except that it cannot involve a formal post-hospital outreach program as described in Table 2. Usual care will thus typically involve the patient undergoing venous blood sampling at their GP surgery or pathology specimen collection centre and the result being reported to the GP, who will then determine the need for dosage adjustments and communicate them back to the patient or carer. Alternative models of usual care may include the patient undergoing POC testing in the GP surgery and receiving immediate dosage adjustment advice during a GP consultation or from the practice nurse, in liaison with the GP; GPs or practice nurses utilising POC monitors during home visits; or mobile phlebotomy services offering venous sampling in the patient's home, with subsequent reporting of the result to the GP and communication of dosing instructions to the patient or carer.

In the control phase of the study, a single home visit for data collection purposes will be conducted by a project officer approximately 8 days post-discharge. At this visit, POC INR monitoring will be performed and data will be collected regarding the patients' warfarin therapy and INR results since discharge, medications and any adverse events.

Three questionnaires will be administered at this visit - the EQ-5D quality of life (QoL) questionnaire, which has been widely used across a number of clinical settings [46,47]; a previously validated warfarin knowledge questionnaire, the Oral Anticoagulation Knowledge (OAK) test [48]; and a modified Tool for Adherence Behaviour Screening (TABS) survey [49]. While TABS was developed in patients with chronic obstructive pulmonary disease, it was designed as a non-specific tool to screen for potential non-adherence in patients with chronic ailments and possesses advantages over other commonly used compliance measures in that it addresses both intentional and unintentional non-adherence and over- and under-utilisation.

A final follow-up will be conducted via telephone and postal questionnaires (EQ-5D, the OAK test, TABS and the disease-specific Duke Anticoagulation Satisfaction Scale (DASS)) [50] approximately 90 days post-discharge. Corroboration of details of any adverse events experienced by the patient and their current medications and INR results will be requested from their GP at this time via a postal form. Non-responders will receive a reminder telephone call or fax after 4 to 8 weeks. For patients experiencing readmission to hospital during their 90 days post-discharge, Australian Refined Diagnosis Related Group (AR-DRG) codes and other details will be obtained from their notes from the relevant hospital's Medical Records Department. The data to be collected at each time point are summarised in Table 3.

**Table 3 T3:** Data collection summary

Data	Time point				
	
	Baseline	Visit 1	Visit 2*	Visit 3^i ^or Day 8^c^	Day 90
Demographics, alcohol intake, smoking history, drug history, height, weight, serum creatinine, haematocrit	✓				

Warfarin therapy details- indication, intended duration, target INR, newly commenced or continuing, heparin pre-treatment, inpatient doses/INRs, doses/INR on discharge, warfarin counselling documented	✓				

Medications, warfarin drug interactions	✓			✓	✓

Medical history	✓				

INR	✓	✓**	✓**	✓**	✓

Warfarin dosing/INR history	✓			✓	✓

Number of GP consultations (since discharge, or between Days 8 and 90)				✓	✓

Adverse events, hospital readmissions				✓	✓

Warfarin continuing, reason for discontinuation		✓	✓	✓	✓

Beyth Bleeding Risk score	✓^C^	✓^I^			

Warfarin dose, changes recommended, visit outcome, visit length, travel time		✓	✓	✓	

QoL (EQ-5D), warfarin knowledge		✓		✓	✓

QoL (Duke Anticoagulation Satisfaction Scale (DASS))					✓

Adherence (Tool for Adherence Behaviour Screening (TABS))				✓	✓

Self-reported health services utilisation					✓

(* Visit 2 if required, ** POC monitoring, ^C ^Control, ^I ^Intervention)

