### Intervention patients

Following recruitment of a patient (as described for the control patients above), the patient's GP will be telephoned by the project officer requesting verbal consent for the patient's participation in the study. Upon receipt of verbal consent, a standard package will be faxed to the GP surgery. This will contain an Information Statement and Consent Form, details of the patient's inpatient warfarin therapy to that time, and a HMR referral form pre-populated by the project officer with information gathered during the patient's hospital admission to expedite the referral process. The GP will be requested to amend or complete any additional information on the HMR referral form, sign and date it, and forward it to the patient's community pharmacy, who will subsequently engage an accredited pharmacist to provide the service. This imitates the existing HMR referral process. The community pharmacy will receive an identical faxed copy of the patient's warfarin therapy details and the contact details of the trained accredited pharmacists in the local geographical area to whom they can refer the patient under the study protocol. Upon the patient's discharge, the project officer will forward the updated INR and warfarin dosing information and discharge drug therapy via fax or email to the GP, community pharmacist and accredited pharmacist.

After discharge from hospital, patients will receive their follow-up home visits, based on a collaborative risk assessment, approximately according to the study protocol detailed in Table 4.

**Table 4 T4:** Timing of post-discharge visits under the 2 levels of service

Level of Service	Number of Days Post-Discharge		
	
	Visit 1	Visit 2*	Visit 3
'Level 1 Service' (2-visit model)	2-3 days	-	7-8 days

'Level 2 Service' (3-visit model)	2-3 days	4-6 days	8-10 days

(* All patients will receive the visits designated as Visit 1 and 3; Visit 2 is the optional additional visit)

## Visit 1

Visit 1 will involve 4 components: the HMR, POC INR monitoring, comprehensive warfarin education or reinforcement of previous education as required, and data collection, including administration of the EQ-5D questionnaire and OAK test. Results of the POC INR monitoring will be communicated to the patient's GP for dose adjustment if necessary. In the interests of patient safety, an INR result above 3.5 will be designated as an indication for immediate GP contact.

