Based on an assessment of the patient's bleeding risk, the GP and accredited pharmacist will collaboratively determine whether the patient will receive 1 (the 'Level 1 Service') or 2 (the 'Level 2 Service') subsequent visits. This risk assessment will be based on calculation of their Beyth Outpatient Bleeding Risk Index (which estimates a patient's risk of major bleeding within 3 and 12 months) [51], INR stability and an overall evaluation encompassing falls risk and drug interaction potential. A previously utilised definition of stability will be utilised: "2 consecutive INR results within the target range or the first measurement in the therapeutic range when the previous or subsequent INR varied by no more than 0.5 INR units outside the target range" [52]. Only patients deemed to be at 'low' or 'intermediate' risk based on the Beyth Outpatient Bleeding Risk Index and with no other risk factors will be candidates for the Level 1 Service. All other patients - those at 'high' risk on the Beyth Outpatient Bleeding Risk Index (due to their high estimated major bleeding risk, or with additional risk factors, as detailed above), will be mandated to receive the Level 2 Service.

## Visits 2 and 3

Visits 2 and 3 will provide opportunities for POC INR monitoring, provision of warfarin education and resolution of any detected drug-related problems. If patients require more frequent INR tests than the service can offer, pathology testing in combination with POC INR testing will be permitted.

At Visit 3, the completion of the service, data will be collected, the TABS survey administered and the EQ-5D questionnaire and OAK test re-administered. The accredited pharmacist will forward a copy of their HMR report and the standard handover document to the patient's GP and community pharmacy. A similar handover document will be given to the patient.

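### Controls have no starting value for EQ-5D or the OAK knowledge test, and the Day 8 OAK comparison sets a second sitting against a first

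*Protocol article*

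**What the plan says.** **Controls.** Under Control patients, the protocol article plans that "a single home visit for data collection purposes will be conducted by a project officer approximately 8 days post-discharge". It continues: "Three questionnaires will be administered at this visit - the EQ-5D quality of life (QoL) questionnaire", then "a previously validated warfarin knowledge questionnaire, the Oral Anticoagulation Knowledge (OAK) test", and a modified TABS survey. EQ-5D and OAK are repeated at about Day 90. No section gives controls either instrument before Day 8.

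**Intervention patients.** Under Visit 1, set by Table 4 at 2-3 days after discharge, the components are the medicines review, INR testing, warfarin education and "data collection, including administration of the EQ-5D questionnaire and OAK test". Under Visits 2 and 3, the last visit has "the TABS survey administered and the EQ-5D questionnaire and OAK test re-administered". Table 4 places that visit at 7-8 days (Level 1) or 8-10 days (Level 2). Day 90 follows the control procedure.

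**Table 3** agrees with the text. The row "QoL (EQ-5D), warfarin knowledge" is ticked at Visit 1, at Visit 3 or Day 8, and at Day 90, but not at Baseline. The Beyth score row, by contrast, has a marked control time point at Baseline and a marked intervention time point at Visit 1.

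**Rank and analysis.** Outcome measures lists quality of life and warfarin knowledge among the other outcomes, below the primary and secondary ones. Statistical analysis plans independent-samples t-tests for most continuous variables and mentions no adjustment for a starting score.

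**The concern.** A comparison of knowledge or quality of life between groups that were not randomised needs to know where each group began. Here only the intervention group has an early value. The study enrols both patients new to warfarin and patients already taking it, who may well differ in what they know. A different mix in the two groups could produce a difference at Day 8 or Day 90 that has nothing to do with the service. Change from a first measurement is available in one group only. An analysis plan written later could not mend this, because a control value that was never collected cannot be recovered.

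The second problem is specific to the knowledge test. At Day 8 the intervention group sits OAK for the second time within about a week, and controls sit it for the first time. Any gain from having seen the questions would be counted as an effect of the service. Knowledge is not incidental here: the Discussion justifies the emphasis on education by the link between patient knowledge and adverse outcomes, and hopes that the study will support national roll-out.

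**Working it through.** There is no stated figure to reproduce. The main check is a count from Table 3, confirmed against the text, followed by an illustration that rests on an assumed retest gain.

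**1. Sittings of EQ-5D and OAK**

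| | Control | Intervention |
|---|---|---|
| Baseline (in hospital) | no | no |
| Visit 1 (Day 2-3) | visit does not exist | yes |
| Day 8 / Visit 3 | yes (about Day 8) | yes (Day 7-8 or 8-10) |
| Day 90 | yes | yes |
| Total sittings | 2 | 3 |
| Earlier sittings at the Day 8 comparison | 0 | 1 |
| Earlier sittings at the Day 90 comparison | 1 | 2 |

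The Visit 1 tick carries no group label. That it applies to intervention patients only follows from the single control home visit at about Day 8.

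**2. Spacing.** From Table 4, the gap between Visit 1 and Visit 3 is 7 - 3 = 4 to 8 - 2 = 6 days at Level 1, and 8 - 3 = 5 to 10 - 2 = 8 days at Level 2. At Day 90 the most recent earlier sitting was 90 - 8 = 82 days before in controls, and 90 - 10 = 80 to 90 - 7 = 83 days before in intervention patients. The contrast between tested and untested patients therefore exists only at Day 8.

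**3. What can be adjusted for.** Table 3 collects at Baseline, in both groups, whether warfarin is new or continuing, whether counselling was documented, demographics and medical history. These are partial stand-ins for starting knowledge and health. Neither the starting OAK score nor the starting EQ-5D is among them.

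**4. How far a retest gain could matter (OAK, Day 8).** The documents give no retest gain. Assume a range of d = 0.10 to 0.20 standard deviations (SD), no true effect, complete questionnaires and the target group sizes from Sample size (160 control; 240 intervention, 120 per level). Then SE = sqrt(1/n1 + 1/n2) in SD units, and the chance of a nominally significant result is P(|Z + d/SE| > 1.96).

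- Control against both levels pooled: SE = sqrt(1/160 + 1/240) = 0.102.
- Control against one level: SE = sqrt(1/160 + 1/120) = 0.121.

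| Assumed gain d | 160 v 240 | 160 v 120 |
|---|---|---|
| 0.10 SD | 17% | 13% |
| 0.15 SD | 31% | 24% |
| 0.20 SD | 50% | 38% |

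The nominal rate is 5%. Statistical analysis specifies a comparison across three groups, so the right-hand column is nearer to the plan. Unreturned or missing questionnaires would lower both columns. The table shows sensitivity to an assumption and does not estimate this trial's error rate.

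**The case against.** The case on the other side is substantial, and much of it stands.

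- **Rank.** Both measures are other outcomes. Major bleeding and every secondary outcome are untouched. A reader might infer that the schedule weakens the trial's main conclusion; nothing in the protocol supports that.
- **EQ-5D.** It asks patients to describe their health and has no answers to learn, so the retest argument belongs to OAK. The missing control starting value affects both instruments.
- **Day 90.** Both groups have by then sat the test before, with a similar gap since the last sitting. The one extra sitting matters less than at Day 8.
- **Adjustment.** It would be too strong to say that prior knowledge cannot be adjusted for at all, or that no gain could be credited to the service. The recorded covariates allow partial adjustment, and a large difference would not be explained away by a modest retest gain.
- **Order within Visit 1.** A reader might infer that the intervention group's first OAK score already reflects the education. The text lists the components of the visit without an order, and a condensed article may leave that to the full protocol. All that can be said is that the score is not assured to precede the education.
- **Consistency.** Text and table agree, so this is an asymmetry in the design and not a contradiction.
- **Protecting usual care.** The Discussion worries about a Hawthorne effect, and a single control visit fits that worry. An in-hospital knowledge test could prompt controls to seek information. This is a real but small cost of the remedy.

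None of this supplies the missing control value, and only collecting it would.

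**Conclusion.** The point holds for two lower-ranked outcomes. It is worth correcting because correction is cheap and cannot be made after the event.

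For both EQ-5D and OAK, controls have no starting value. In this non-randomised comparison, differences at Day 8 and Day 90 therefore cannot be adjusted for the starting score and can be only partly adjusted through other baseline data. This conclusion rests on the schedule alone.

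For OAK at Day 8 there is in addition one earlier sitting against none, so any retest gain would favour the service. Its size is unknown. The percentages under the working depend wholly on an assumed gain and should not be read as the trial's false-positive rate. The effect is weaker at Day 90 and hardly applies to EQ-5D.

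**What to change.** In Table 3, replace the Visit 1 tick for EQ-5D and warfarin knowledge with a Baseline tick for both groups, and amend the Control patients and Visit 1 text to match. The project officer, who already recruits patients in hospital, would give both instruments there. Each group then has three sittings (Baseline, Day 8 or Visit 3, Day 90), and the first precedes the service in everyone. Compare the groups at Day 8/Visit 3 and at Day 90 with a linear model adjusted for the baseline score. This will not remove every difference between non-randomised groups, but it deals with the most direct one.

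Costs: a few more minutes at recruitment for controls, and no additional sitting for intervention patients. An inpatient EQ-5D will partly reflect the acute illness, though it can still serve as a covariate. The knowledge test may slightly prime controls; the priming would then apply to both groups, but could move the comparator a little away from usual care. The study would also give up a score taken at the start of the home service itself.

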### Intervention patients

Following recruitment of a patient (as described for the control patients above), the patient's GP will be telephoned by the project officer requesting verbal consent for the patient's participation in the study. Upon receipt of verbal consent, a standard package will be faxed to the GP surgery. This will contain an Information Statement and Consent Form, details of the patient's inpatient warfarin therapy to that time, and a HMR referral form pre-populated by the project officer with information gathered during the patient's hospital admission to expedite the referral process. The GP will be requested to amend or complete any additional information on the HMR referral form, sign and date it, and forward it to the patient's community pharmacy, who will subsequently engage an accredited pharmacist to provide the service. This imitates the existing HMR referral process. The community pharmacy will receive an identical faxed copy of the patient's warfarin therapy details and the contact details of the trained accredited pharmacists in the local geographical area to whom they can refer the patient under the study protocol. Upon the patient's discharge, the project officer will forward the updated INR and warfarin dosing information and discharge drug therapy via fax or email to the GP, community pharmacist and accredited pharmacist.

After discharge from hospital, patients will receive their follow-up home visits, based on a collaborative risk assessment, approximately according to the study protocol detailed in Table 4.

**Table 4 T4:** Timing of post-discharge visits under the 2 levels of service

Level of Service	Number of Days Post-Discharge		
	
	Visit 1	Visit 2*	Visit 3
'Level 1 Service' (2-visit model)	2-3 days	-	7-8 days

'Level 2 Service' (3-visit model)	2-3 days	4-6 days	8-10 days

(* All patients will receive the visits designated as Visit 1 and 3; Visit 2 is the optional additional visit)

## Visit 1

Visit 1 will involve 4 components: the HMR, POC INR monitoring, comprehensive warfarin education or reinforcement of previous education as required, and data collection, including administration of the EQ-5D questionnaire and OAK test. Results of the POC INR monitoring will be communicated to the patient's GP for dose adjustment if necessary. In the interests of patient safety, an INR result above 3.5 will be designated as an indication for immediate GP contact.

Based on an assessment of the patient's bleeding risk, the GP and accredited pharmacist will collaboratively determine whether the patient will receive 1 (the 'Level 1 Service') or 2 (the 'Level 2 Service') subsequent visits. This risk assessment will be based on calculation of their Beyth Outpatient Bleeding Risk Index (which estimates a patient's risk of major bleeding within 3 and 12 months) [51], INR stability and an overall evaluation encompassing falls risk and drug interaction potential. A previously utilised definition of stability will be utilised: "2 consecutive INR results within the target range or the first measurement in the therapeutic range when the previous or subsequent INR varied by no more than 0.5 INR units outside the target range" [52]. Only patients deemed to be at 'low' or 'intermediate' risk based on the Beyth Outpatient Bleeding Risk Index and with no other risk factors will be candidates for the Level 1 Service. All other patients - those at 'high' risk on the Beyth Outpatient Bleeding Risk Index (due to their high estimated major bleeding risk, or with additional risk factors, as detailed above), will be mandated to receive the Level 2 Service.

## Visits 2 and 3

Visits 2 and 3 will provide opportunities for POC INR monitoring, provision of warfarin education and resolution of any detected drug-related problems. If patients require more frequent INR tests than the service can offer, pathology testing in combination with POC INR testing will be permitted.

At Visit 3, the completion of the service, data will be collected, the TABS survey administered and the EQ-5D questionnaire and OAK test re-administered. The accredited pharmacist will forward a copy of their HMR report and the standard handover document to the patient's GP and community pharmacy. A similar handover document will be given to the patient.

Day 90 follow-up will be conducted for these patients as described for the control phase. In addition, stakeholders immediately involved with this service (patients, GPs, community and accredited pharmacists) will be surveyed to assess their satisfaction with the service and identify its perceived advantages, deficiencies and suggested improvements to the process to inform its future evolution and implementation. A structured postal questionnaire will be included with the Day 90 data collection forms for intervention patients to complete regarding their experience. The GPs, community pharmacists and accredited pharmacists will be surveyed at the completion of the recruitment period.

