### Justification for this trial

While the previously described RCT was highly successful, it involved only 1 dedicated pharmacist researcher and a limited geographical area. In considering national implementation of the service, the intensity of the 4-visit model may not prove sustainable; thus, a trial investigating 2-visit and 3-visit models is considered necessary. It is also hoped that by integrating the warfarin management service into the existing Home Medicines Review (HMR) program, funded by the Australian Government Department of Health and Ageing and described below, sustainability of the service will be assured.

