### Sample size

Based on sample size calculations, groups comprising approximately 120 patients in each (control, 2-visit model, and 3-visit model) are estimated as being statistically adequate. This is based on the previous RCT of this model of care where 10% of the usual care group experienced a major bleeding event within 90 days post-discharge, which was reduced to 2% in the intervention group [36]. Using these figures, approximately 108 patients are needed per group at a power of 80% and p = 0.05. Published data are also available indicating that approximately 30-40% of patients commenced on warfarin experience a bleeding complication within 3 months [16,18,36,45]. The aim of the intervention program is to reduce this figure to below 10%, in which case approximately 72 patients are needed per group at a power of 80% and p = 0.05. The proposed recruitment targets are thus 160 in the control group and 240 in the intervention group (120 receiving the 2-visit model and 120 the 3-visit model).

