### Statistical analysis

Demographic data will be utilised to compare the control and intervention groups for a range of parameters (e.g. age, gender, PhARIA class, living and medication management arrangements, co-morbidities, warfarin drug interactions) using independent samples t-testing for continuous data and chi-squared analysis for categorical data. Outcome data will be reported using parametric statistics, with independent samples t-testing utilised for the majority of continuous variables and chi-squared analysis for the majority of discrete variables. Data will be statistically analysed across the 3 groups (control, Level 1 Service, and Level 2 Service). For the evaluation questionnaires, responses will be recorded on modified Likert scales, with 0 representing "Strongly agree" and 10 "Strongly disagree". Qualitative feedback will obtained via open-ended questions. Data analysis will involve descriptive statistics and thematic analysis of the qualitative responses.

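### Service level is assigned by bleeding risk, so comparing Level 1 and Level 2 with each other or with an undivided control group mixes patient risk with service effect

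*Protocol article*

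**What the plan says.** All statements are from the protocol article.

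- **How the level is set** (Intervention patients, Visit 1): "Based on an assessment of the patient's bleeding risk, the GP and accredited pharmacist will collaboratively determine" whether one or two further visits follow. The inputs are the Beyth index, INR stability, falls risk and drug interaction potential. Patients at low or intermediate Beyth risk "with no other risk factors will be candidates for the Level 1 Service"; all others "will be mandated to receive the Level 2 Service".
- **What the index measures** (same section): it is the score "which estimates a patient's risk of major bleeding within 3 and 12 months". The primary outcome is major bleeding within 90 days of discharge.
- **Controls** (Subjects; Control patients): they enter under the same general eligibility criteria and are not divided by risk.
- **Analysis** (Statistical analysis): "Data will be statistically analysed across the 3 groups (control, Level 1 Service, and Level 2 Service"), mainly by t-tests and chi-squared tests. The baseline comparison described there is control versus intervention, not level by level.
- **Targets** (Sample size): 160 controls and "240 in the intervention group (120 receiving the 2-visit model and 120 the 3-visit model").
- **Purpose** (Justification for this trial): because four visits may not be sustainable, "a trial investigating 2-visit and 3-visit models is considered necessary".

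**The concern.** The level a patient receives depends on a predictor of the primary outcome. Level 1 is a selected lower-risk group, Level 2 is the remainder, and the control group contains both kinds of patient. A difference between a level and the controls, or between the two levels, therefore reflects who was put there as well as what they received. A larger sample does not remove this.

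The direction is predictable: the lighter service is flattered and the heavier one penalised. The trial is meant to inform a national roll-out, and a reader of three-group results would naturally use them to choose between two and three visits. The Discussion defends the lack of randomisation only for control versus intervention and does not address selection between levels. The 120/120 targets also treat the split as something the design controls, whereas the risk mix of the patients decides it.

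**Working it through.** **The plan's own figure.** The stated 108 per group for 10% versus 2% at 80% power is reproduced by a one-sided test without continuity correction; the two-sided figure is 138. That is a separate matter. The plan gives no figure for bias between levels, so the check below is an illustration.

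**Inputs from the document.** Control bleeding 10%; intervention 2%, an 80% reduction; group sizes 160, 120 and 120.

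**Assumptions, not in the document.** The service has no effect, overall bleeding is 10% in both phases, half the patients are high-risk, and Level 2 patients bleed *k* times as often as Level 1 patients.

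**Step 1: expected rates.** From 0.5 × low + 0.5 × *k* × low = 0.10, low = 0.10 / (0.5 + 0.5*k*) and high = *k* × low. For *k* = 3, low = 0.10 / 2 = 5.0% and high = 15.0%.

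**Step 2: how often a useless service gives p < 0.05.** Two-sided Pearson chi-squared test, exact enumeration of the binomial outcomes:

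| *k* | Level 1 rate | Level 2 rate | Level 1 vs control (120 vs 160) | Level 2 vs control (120 vs 160) | Level 1 vs Level 2 (120 vs 120) | Pooled vs control (240 vs 160) |
|---|---|---|---|---|---|---|
| 1 | 10.0% | 10.0% | 5% | 5% | 5% | 5% |
| 1.5 | 8.0% | 12.0% | 9% | 9% | 18% | 5% |
| 2 | 6.7% | 13.3% | 17% | 15% | 42% | 5% |
| 3 | 5.0% | 15.0% | 35% | 26% | 76% | 5% |
| 5 | 3.3% | 16.7% | 62% | 39% | 96% | 5% |

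The single three-group chi-squared test, simulated 8,000 times, was significant in about 31%, 64% and 91% of trials for *k* = 2, 3 and 5.

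**Step 3: a different risk mix.** With 20% high-risk patients, *k* = 2 and the group sizes kept, Level 1 versus control rejects in 7.5% of trials and Level 2 versus control in 39%. The distortion moves from one contrast to the other.

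**Step 4: a service that works.** With an 80% reduction in everyone and *k* = 3, Level 1 shows 0.2 × 5.0% = 1.0% and Level 2 shows 0.2 × 15.0% = 3.0%. Two visits look better than three although the relative benefit is identical. For Level 2 merely to match the 10% control rate, the service must cut risk by 1 − 0.10/high, which is 25%, 33% and 40% for *k* = 2, 3 and 5.

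**The case against.** The strongest reply is that the protocol describes one risk-tiered service. Allocating visits by risk is then the intervention, not a failed randomisation, and neither the Justification nor the Objectives states a superiority question of two versus three visits. The pooled contrast is already implied: the Abstract and the Overview speak of outcomes with the service against usual care, and the sample size section names an intervention group of 240. This stands, and it limits the damage to the level-specific contrasts. It does not excuse them, because the analysis section does name the three groups.

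Five stronger readings are tempting, and the document does not support them:

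- *The contrasts measure risk and not the service.* They mix the two, and the design cannot separate them.
- *Level 1 will look protective and Level 2 harmful.* This holds only in expectation, with no or little effect and an assumed risk ratio. With the planned 80% reduction and *k* = 3, Level 2 shows 3.0% against 10% in controls.
- *The effectiveness question is lost.* The pooled comparison is untouched by the split.
- *The Beyth score is not comparable between groups.* Table 3 records the "Beyth Bleeding Risk score" at Baseline in controls and at Visit 1 in intervention patients. The visit is only 2 to 3 days after discharge, and history, creatinine and haematocrit are collected at Baseline for everyone.
- *Newly started patients are steered to Level 2 by the INR-stability criterion.* This is plausible, but no figure shows how many would fail that criterion.

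Nor is the absence of a named adjustment method a fault in itself: this is a condensed article, and its wording leaves room for other methods. The point rests only on the three-group analysis that is stated.

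**Conclusion.** The point holds for Level 1 versus control, Level 2 versus control and Level 1 versus Level 2. Each is confounded by indication under the protocol's own rule, biased in expectation for the 2-visit model and against the 3-visit model, and none can support a conclusion about the number of visits. The direction requires only that the risk assessment predicts bleeding, which is why it is used. The size depends on the risk ratio and the high-risk share, neither of which the document gives: over ratios of 1.5 to 5 with an even split, false-positive rates run from modest (9% and 18%) to severe (62% and 96%). Pooled intervention versus control keeps its nominal 5% with respect to this problem, subject to the usual limits of a non-randomised comparison.

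**What to change.** In the Statistical analysis section:

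1. Name all intervention patients (240) versus all controls (160) as the primary effectiveness comparison.
2. Replace the level-versus-control contrasts with secondary comparisons within the same Beyth category, low/intermediate against low/intermediate and high against high, whatever level was received. Compute the index from baseline data in both groups. Grouping by baseline category avoids selection by level, including the judgement-based part of the Visit 1 decision that has no counterpart in controls.
3. Label Level 1 versus Level 2 as descriptive only.

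In the Sample size section, call 120/120 an expected split and not a target.

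The allocation of visits does not change and no new data are needed. The cost is power. With half the patients high-risk, each stratum has 160/2 = 80 controls and 240/2 = 120 intervention patients. With the planned 80% reduction and *k* = 2, 3 and 5, exact power is about 54%, 42% and 28% in the low/intermediate stratum and 83%, 87% and 90% in the high stratum, against 94% pooled. The trial also gives up a 2-visit versus 3-visit claim, which its design cannot support.
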